Tertiary objectives include evaluating both self-reported and objectively measured physical activity for parents as well as parent-child co-activity (via accelerometry using a Bluetooth enabled proximity tagging feature). It is hypothesized that parents in the habit formation condition will show higher light and moderate intensity PA compared to the other conditions due to consistent performance of co-activity with their children.

Additional parental factors such as quality of life, parental competence, and family functioning will also be examined. We hypothesize that conditions that increase PA will show commensurate increases in these factors. Finally, exploratory analyses will focus on seasonal, or gender differences across primary outcomes by assigned condition [47, 48].

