### Recruitment procedure

The recruitment methods of this study follow a previously refined recruitment strategy similar to published protocols conducted within the same laboratory [54, 55]. The primary means of recruitment are targeted advertisements on online interest sites (blogs, parent resource websites, and classifieds) and social media platforms (Facebook, Instagram). For social media posts, the visual and written content are geared toward families. Posts are also targeted to a local parent audience by selecting restrictions for age range, keywords, and interests. A small fee applies these demographic filters and allows the ad to run for about 7 days. Posts are also manually shared to relevant Facebook groups (e.g., parent groups). In addition, posters are regularly placed around the Greater Victoria region at locations such as daycares and preschools, community centres, recreation centres, local coffee shops, and health care centres. Twice a month, a designated Recruitment Officer also offers pamphlets and study information through stalls at family-oriented events such as community markets. In order to ensure a diverse study population, facilities from each region of the city were systematically selected and contacted for recruitment. Recruitment also takes place through word of mouth, whereby current participants refer the study to others by passing on information. Incentives for participation include honoraria at each respective assessment to compensate participants for their time ($25 per family, increasing by $5 increments at each assessment for a total $130 across the study).

Recruitment is rolling across the duration of the study. Families interested in partaking are invited to contact the researchers via email or phone. Upon receipt of inquiries, potential participants are sent additional study details over email and are invited to schedule a phone call. Next, a Recruitment Officer formally screens potential participants over the phone. If they are deemed eligible, they are scheduled for a baseline assessment. Written informed consent is obtained from parents and verbal assent is obtained from children before study enrolment.

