
### Outcome measures

#### Primary outcome measures

The primary outcome of child MVPA will be assessed with the Actigraph wGT3X-BT Activity Monitor using validated seven-day accelerometry methods for preschoolers. Measurements will take place at baseline, 6 weeks, 3 months, and 6 months (primary endpoint of interest) and MVPA will be evaluated as change from baseline. Currently, the analysis plan is to use the established cut-points and accelerometer best practices outlined below, however the research team recognizes that accelerometer analysis in an ever-changing discipline, therefore we will be responsive to these advances by using the most validated cut-points at the time of study closure. At present, it is anticipated that the MVPA of children will be determined using the cut-points for young children recommended by Janssen and colleagues [63]. These cut-points define moderate to vigorous activity as ≥420 counts per 15 s (≥1680 counts per minute (CPM)). These cut-points have shown fair to excellent validity in preschoolers when compared to direct observation [63].

Children are instructed to wear the device during waking hours for a minimum of 10 h a day for 7 consecutive days (5 weekdays, and 2 weekend days). It is secured by an elastic band and worn around the waist above the right hip. Because the devices are not waterproof, participants are advised to remove them for any water-based activities. In addition, participants are provided with a logbook and parents are asked to note any removals for water activities, record unusual circumstances (e.g., changes to routine such as illness), and make notes with particulars such as structured activity.

To initialize and download the accelerometers as well as analyze the data, ActiLife software version 6.11.9 [64] is used. The devices are initialized to collect data at a 30 Hz sample rate and are downloaded into 15-s epochs in order to capture the sporadic nature of movement in young children and based on common practice for preschooler accelerometry [65, 66]. Data will be included for analysis if children have at least 4 days of valid wear time per week [67–69]. For a day to be considered valid there will need to be a minimum of 300 min (6 h) during waking hours [70]. Non-wear time is defined as ≥20 min of consecutive zero counts or the equivalent of ≥80 consecutive 15-s intervals of zero counts [69, 71]. It is assumed that this non-wear time algorithm captures daytime naps.

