### Analysis strategy

For each outcome, the pattern of missing data will be evaluated to determine an appropriate analytical strategy [102], after which the normality of all variables will be examined to determine whether transformations will be required. The first set of analyses will make preliminary demographic comparisons among adherers to the study versus dropouts to determine the representativeness of the sample. Next, to address the primary objective (i.e., to determine whether the minutes / day of MVPA change over time similarly for all three conditions, hierarchical linear modeling [103] will be used. Specifically, Level-1 of the model will include an intercept (i.e., the baseline PA) and slope (i.e., to examine potential change over the 4 assessment periods) that will be predicted by Level-2 covariates (i.e., demographics). Additionally, dummy variables will be created for condition (Habit formation group: 1 = yes or 0 = no; Planning group: 1 = yes or 0 = no; Education control: 1 = yes or 0 = No) at Level-2 with the Habit Formation and Planning group variables being added to the model to predict the intercept and slope at Level-1. In doing so, the control group is compared against the other two groups to determine if baseline MVPA is similar across conditions and whether the change in MVPA is similar across conditions. Follow-up analyses will be conducted for the Habit Formation vs. Planning group comparison. To address the secondary objective (i.e., to determine whether the change in the underlying motives explain the potential change in MVPA during the intervention similarly for all 3 groups), a time varying covariate mediation analysis will be used [104]. Briefly, the analyses needed to establish mediation will treat the underlying motives as time varying covariates at Level-1 of the model. Then, the dummy coded condition variables will be entered at Level-2 to determine if the Level-1 motives mediate the condition / MVPA relationship. Finally, to determine whether there is a seasonal, intergenerational, or gender difference across the primary and secondary outcomes (i.e., to address the tertiary objectives), each variable will be entered into the various models at Level-2 to predict the intercepts and slopes at Level-1. Doing so will determine if they impact the change in the various outcomes across time.

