### Justification of sample size

G-Power (Version 3.1.9.2) was used to calculate sample size. With 4 repeated assessments, 3 groups, a power of .90, an alpha of .05, effect sizes ranging from .25 to .30, and an anticipated attrition rate of 15% [34], a minimum of 165 families with a goal of 240 families (i.e., 55–80 families per condition) are needed to show a significant difference in physical activity accelerometry (minutes of MVPA primary outcome) by condition over time. The effect sizes represent the findings from our prior intervention research comparing planning to education with this demographic [34] and considering our pilot study on habit formation [42], yet it is clearly in the clinically meaningful range for the detection of differences between the planning and habit formation conditions [107, 108]. However, detection is dependent on the performance of the habit versus planning conditions which is largely unknown.

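### The exploratory aim asks whether season or gender changes the condition effect, but the stated model has no term for this, and one Level-2 value describes season only in part

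*Protocol article*

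**What the plan says.** Under Study objectives and hypotheses, the last stated aim is that "exploratory analyses will focus on seasonal, or gender differences across primary outcomes by assigned condition".

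Analysis strategy describes a two-level growth model for MVPA. Level-1 holds an intercept and a slope over the four assessments. The two condition dummies sit at Level-2, "with the Habit Formation and Planning group variables being added to the model to predict the intercept and slope at Level-1". For season, generation and gender the plan is that "each variable will be entered into the various models at Level-2 to predict the intercepts and slopes at Level-1", and it states what this delivers: "Doing so will determine if they impact the change in the various outcomes across time". Condition does not appear in that sentence.

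Three other statements bear on season:
- Recruitment procedure: "Recruitment is rolling across the duration of the study".
- Primary outcome measures: child MVPA is measured at baseline, 6 weeks, 3 months and 6 months, the last being the primary endpoint.
- Analysis strategy, on the mediation model: the analyses will "treat the underlying motives as time varying covariates at Level-1 of the model". The plan thus already uses time-varying covariates, but not for season.

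**The concern.** The aim and the analysis address different questions. The aim is about effect modification: does the benefit of habit formation or planning depend on the child's gender or on the season? The analysis is about main effects on change: do boys and girls, or children with different season values, follow different trajectories whatever their arm? Anyone who follows Analysis strategy to the letter would report the second as the answer to the first.

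Season raises a further, smaller matter. Families enter throughout the year and are followed for six months, so season differs between a child's own visits. A Level-2 variable has one value per child. It can carry season of enrolment, and through the slope a straight-line seasonal trend, but not the season in which each wear week fell. Seasonal variation that it misses stays in the residual.

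**Working it through.** **Moderation.** The article gives no figure to reproduce, so the check is to write out the model it describes. With one moderator M added:

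- slope = g0 + g1·Habit + g2·Planning + g3·M
- habit minus education at M = 0: g1
- habit minus education at M = 1: (g1 + g3) − g3 = g1

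The contrast is g1 at every value of M, and likewise g2 for planning. No parameter lets it vary. A product is needed, for example g4·Habit·M + g5·Planning·M in the slope, which is a condition × M × time term.

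To see what g3 picks up, assume that the habit effect at 6 months differs by 10 min/day between the sexes, that the other two arms show no sex difference, and that the arms are equal in size. Then g3 averages (10 + 0 + 0)/3 = 3.3 min/day. An illustrative simulation agrees (165 families, 200 replicates, assumed between-child SD 12 and residual SD 10 min/day). The coefficient as written averaged 3.4 and the three-way coefficient 9.2. The three-way term was significant in only 0.345 × 200 = 69 replicates, so even a large difference would often be missed.

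**How far season varies within a child.** Assume enrolment uniform over the year. The share of children in a different season from baseline is the time since baseline divided by the season length, up to one season length:

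| Visit | Quarters (3 months) | Half-years (6 months) |
|---|---|---|
| 6 weeks | 1.5/3 = 50% | 1.5/6 = 25% |
| 3 months | 3/3 = 100% | 3/6 = 50% |
| 6 months | 100% (two quarters on) | 6/6 = 100% |

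**What season of enrolment at Level-2 can capture.** Assume a yearly sine of amplitude A, visits at weeks 0, 6, 13 and 26, and uniform enrolment.

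- The shift from baseline to 6 months is A·cos(x + π) − A·cos(x) = −2A·cos(x). It runs from −2A to +2A with SD 2A/√2 = 1.41A. With A = 5 min/day (an assumption) the SD is 7.1 min/day.
- Four enrolment categories, each with its own intercept and straight line, leave 34.5% of the seasonal variance over all four visits, so they capture about 65%. This holds wherever the quarters are cut.
- For the baseline-to-6-month shift alone, the four category means explain [sin(π/4)/(π/4)]² = 0.900² = 81% and leave 19%. This is the most that enrolment quarter can explain. A line fitted through all four visits need not reach it.
- Two enrolment categories leave between about 47% and 88% over all visits, depending on where the boundary falls relative to the seasonal peak.
- Sine and cosine of the assessment date at Level-1 remove all of it under this pattern.

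**Effect on the primary comparison.** Randomisation balances season between arms in expectation, so no bias follows. The chance difference between two arms of 55 (the article's minimum) in mean seasonal shift has SD 7.1 × √(2/55) = 1.3 min/day at A = 5. In the same simulation with A = 10, replacing enrolment half-year at Level-2 by the half-year of each visit at Level-1 lowered the residual variance from about 122 to 113, or 9/122 = 7%.

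**The case against.** The best defence is that season of enrolment is a legitimate Level-2 variable. With a fixed visit schedule it largely determines the season of every later visit. Letting it predict the slope is how a growth model shows that families enrolled at one time of year tend to rise and those enrolled at another tend to fall. This stands. A reader might infer that Level-2 season is simply wrong, or that season changes at every visit. Neither is supported: four categories capture most of the seasonal variance, and at 6 weeks half of the children (quarters) or three quarters (half-years) are still in their baseline season. What remains is that the article does not say that season of enrolment is meant, and that a straight line captures the pattern only in part.

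It can also be said that Analysis strategy restates the aim without reference to condition, that the variables go into models already holding the condition dummies, and that exact interaction terms for an exploratory aim are usually left to the full plan. The last point would excuse silence, but the article is not silent. It fixes how the variables enter and says what the result will show, and that is not the question in the objectives. Sharing a model with the condition dummies does not create an interaction.

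Finally, three-way terms at 55 to 80 families per arm will be imprecise. That is true, and a reason to say so in the report. It is not a reason to report a different coefficient.

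**Conclusion.** The mismatch between aim and model holds, and it follows from the article's wording alone. As specified, the analysis cannot show whether the condition effect differs by gender or season. Its consequence is limited because the aim is exploratory.

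The season part holds in a weaker form. One Level-2 value represents season of enrolment with a linear trend. With four categories that leaves about a third of the seasonal variance and at least 19% of the baseline-to-6-month shift; with two categories it leaves more, depending on the cut point. These shares rest on an assumed yearly sine and uniform enrolment. The size in minutes depends on a seasonal amplitude that the article does not give.

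A reader might go on to infer that the primary comparison is biased by season. The documents do not support that: allocation is random, so season adds noise, and chance imbalance is already reflected in the standard error. Modelling season better would gain precision, of unknown and possibly modest size. Nor is anything wrong with gender at Level-2. All it lacks is the cross with condition.

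**What to change.** In Analysis strategy:

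1. For the exploratory aim, add condition × gender × time and condition × season × time terms with their lower-order terms, and report those interactions with confidence intervals as the result. For season, a post-baseline indicator can replace time. A plain condition × season term would not do, because baseline visits carry no intervention effect and would dilute the coefficient.
2. State that these estimates will be imprecise at 55 to 80 families per arm.
3. Define season as season of each assessment, and enter it as a Level-1 time-varying covariate in the MVPA models, for example as yearly sine and cosine of the wear date.
4. Keep gender at Level-2.

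The cost is a change of wording and two further parameters in the primary model if sine and cosine are used. The accelerometer records are time-stamped, so no new data are needed. The revised wording should be settled before outcomes are compared by arm.

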### Justification of sample size

G-Power (Version 3.1.9.2) was used to calculate sample size. With 4 repeated assessments, 3 groups, a power of .90, an alpha of .05, effect sizes ranging from .25 to .30, and an anticipated attrition rate of 15% [34], a minimum of 165 families with a goal of 240 families (i.e., 55–80 families per condition) are needed to show a significant difference in physical activity accelerometry (minutes of MVPA primary outcome) by condition over time. The effect sizes represent the findings from our prior intervention research comparing planning to education with this demographic [34] and considering our pilot study on habit formation [42], yet it is clearly in the clinically meaningful range for the detection of differences between the planning and habit formation conditions [107, 108]. However, detection is dependent on the performance of the habit versus planning conditions which is largely unknown.

### Oversight, data monitoring, ethics, dissemination

#### Data management and confidentiality

Confidentiality procedures are outlined in the consent form and explained by the Research Assistant at the baseline assessment during the informed consent procedure. Participants are provided with unique identifiers and assured that data will be published as group data. Contact information is required but carefully protected: hard copies of any documentation are kept in a locked and secure environment at the University of Victoria. Any data or personal information stored on computers is kept on a secure server. Questionnaire data are stored on SurveyMonkey servers in Canada. If participants withdraw, they may choose whether their data will be used or destroyed. The research team determined a formal data monitoring committee was not necessary. In lieu, the Project Coordinator provides monthly reports on trial progress, participant numbers, and data quality to the Principal Investigator. Project oversight is the responsibility of the Principal Investigator, and therefore the decision to terminate the trial rests with them. Finally, access to the final dataset will be made to the Principal Investigator.

#### Research ethics processes and monitoring

If modifications or amendments to the protocol are required, the Project Coordinator will submit the necessary paperwork to HREB at the University of Victoria. Upon approval, the appropriate updates will be made to the trial registration on the Clinical Trials Registry. There are no anticipated harms that will result from participation. In the case of unintended effects or adverse events, participants are provided with contact information and are instructed to inform the Project Coordinator, the Primary Investigator, or HREB. In the instance of any such events, the research team is trained in documenting and reporting procedures and the safety of all parties is prioritized at all times.

#### Dissemination plans

Trial results will be widely disseminated by way of knowledge exchange activities, such as presentations at academic conferences and publications in relevant journals. Eligibility for authorship in subsequent publications is available to all those who have contributed to the design and protocol of the trial. Findings from this trial could have important implications for public health. For example, results could inform initiatives to improve PA among families with young children. In line with HREB approval, the participant data set will not be accessible for the public. At present, there are no arrangements to make the statistical code available to the public. Results from the trial will be communicated to participants.

## Discussion

To date, we have obtained ethical approval, registered the trial, and have recruited 106 families from the Greater Victoria region. Ethical approval was received from the University of Victoria Human Research Ethics Board. We currently anticipate recruitment will be complete by August 2022. From the 106 parents assessed for eligibility, 94 have completed all of the baseline measures, 49 have completed the six-week measures, and 47 have completed the 3 month measures, and 44 have completed the 6 month measures and exit interview concluding the study (see Fig. 2 for Participant Flow Diagram). The study is ongoing and data collection will continue through 2021 (with the possibility of extending into 2022).

**Fig. 2 Fig2:**
[figure not shown]
Participant Flow Diagram (Clinical Trial Registration Number: NCT03055871)

This protocol describes the implementation of a randomized trial investigating the efficacy of planning and habit interventions aimed at increasing parent-child co-activity. This research is conceptually guided by the M-PAC framework [35]. One anticipated challenge may be the differentiation between those who develop habits naturally as a consequence of repeated planning from those who develop habit from direct intervention in our study. Specifically, M-PAC outlines that habits can form from as a natural extension of self-regulatory planning, under conditions where context repetition is observed over time [109], and this has also been noted by other habit researchers (e.g., [39, 43]. We expect that our direct intervention condition would facilitate for faster changes in habit strength in this case, but we will explore this possibility of direct and indirect habit formation. Our intervention success may also be challenged by the length of the trial. While 6 months duration has been sufficient to produce changes in PA habit strength among adults [38], the dynamics involved in a family system with multiple stakeholders in the intervention may be more challenging when attempting to create the context repetition stability [110] necessary to form a habit. Our qualitative feedback from the intervention will be instrumental in understanding the complexities of this approach in a family system.

Findings from this trial could contribute to the understanding of strategies to increase child PA through targeting parent-child co-activity. This information could prove useful for public health initiatives aimed at improving PA participation among children and families.

